## Abstract

**Background:**

To improve the oral health of low-income children, innovations in dental delivery systems are needed, including community-based care, the use of expanded duty auxiliary dental personnel, capitation payments, and global budgets. This paper describes the protocol for PREDICT (Population-centered Risk- and Evidence-based Dental Interprofessional Care Team), an evaluation project to test the effectiveness of new delivery and payment systems for improving dental care and oral health.

**Methods/Design:**

This is a parallel-group cluster randomized controlled trial. Fourteen rural Oregon counties with a publicly insured (Medicaid) population of 82,000 children (0 to 21 years old) and pregnant women served by a managed dental care organization are randomized into test and control counties. In the test intervention (PREDICT), allied dental personnel provide screening and preventive services in community settings and case managers serve as patient navigators to arrange referrals of children who need dentist services. The delivery system intervention is paired with a compensation system for high performance (pay-for-performance) with efficient performance monitoring. PREDICT focuses on the following: 1) identifying eligible children and gaining caregiver consent for services in community settings (for example, schools); 2) providing risk-based preventive and caries stabilization services efficiently at these settings; 3) providing curative care in dental clinics; and 4) incentivizing local delivery teams to meet performance benchmarks. In the control intervention, care is delivered in dental offices without performance incentives. The primary outcome is the prevalence of untreated dental caries. Other outcomes are related to process, structure and cost. Data are collected through patient and staff surveys, clinical examinations, and the review of health and administrative records.

**Discussion:**

If effective, PREDICT is expected to substantially reduce disparities in dental care and oral health. PREDICT can be disseminated to other care organizations as publicly insured clients are increasingly served by large practice organizations.

**Trial registration:**

ClinicalTrials.gov NCT02312921 6 December 2014. The Robert Wood Johnson Foundation and Advantage Dental Services, LLC, are supporting the evaluation.

## Background

Dental caries (tooth decay) predominantly afflict low-income children [1] who also receive fewer dental services [2]. Approximately 45 % of children 3 to 5 years old and fewer than 10 % of children younger than 2 years old received dental services in 2008 in the United States [2]. Many children have their first dental visit in the Emergency Department, and surgical in-hospital treatment of dental caries is becoming more common and costly. Indeed, preventable dental conditions were the primary reason for 830,590 ED visits by Americans in 2009, a 16 % increase from 2006 [3].

Medicaid is the public health insurance program for low-income children in the United States. It is funded by the federal government and states and administered by states. Most Medicaid dental programs operate on a fee-for-service model. These programs largely fail to reduce access disparities because they provide services for those who access care independent of need and because fees are often very low. Where there are managed care systems, they often graft the same limited model with low capitated payments that incentivize less care. In addition, both approaches focus on open-ended budgets versus global payments and office-based versus community-based care. The United States government Centers for Medicaid and Medicare Services expects to move away from the traditional “fee-for-service” system to one based on global budgets, capitation payments, and pay for performance [4]. A recent Cochrane review identified only two studies, both European, on the effects of financial incentives on the delivery of primary dental care [5]. Neither study examined risk-based capitation programs or community-based care systems. Conrad and Perry reviewed the effect of financial incentives on physician behavior and reported that comprehensive financial incentives (for example, balancing rewards and penalties; blending structure, process, and outcome measures; emphasizing continuous, absolute performance standards) offer the prospect of significantly enhancing quality beyond the modest impacts of prevailing pay-for-performance programs [6]. From these reviews, it is also clear that no one has tried to incentivize the entire dental team. Community-based auxiliaries, outreach personnel, case managers, and other practice staff are essential to identify children at risk and to ensure they receive intensive and appropriate management.

### Aims and objectives

To improve the oral health of Medicaid-enrolled children, dental delivery systems innovations are needed, including community-based care, the use of expanded duty auxiliary dental personnel [7, 8], capitation payments, and global budgets [6, 9]. The project aim is to implement and evaluate the PREDICT (*Population-centered Risk- and Evidence-based Dental Interprofessional Care Team*) dental care system. The primary objective is to determine the effectiveness of the new model on decreasing dental caries in Medicaid-enrolled children, pregnant women and new mothers. The secondary objectives are to determine the impact of PREDICT on access, quality, equity and cost.

## Methods/Design

This protocol follows the SPIRIT [10], CONSORT [11] and SQUIRE [12] statements and relevant extensions [13, 14]. The main research question is: Do new delivery and payment systems (compared with the current system) reduce the prevalence of untreated dental caries, and improve access, quality and equity of care for Medicaid-enrolled children, pregnant women and new mothers?

### Design, setting and selection

#### Study design

The study is a cluster parallel-group randomized controlled trial.

#### Setting

The study setting is 14 rural counties in Oregon, USA served by a dental care organization, Advantage Dental Services (ADS), LLC, Redmond, Oregon. ADS is the largest provider of Medicaid dental services in Oregon. It serves about 318,000 members statewide. The organization provides services in 187 primary care and 95 specialist private practices, and 34 staff-model ADS-owned dental clinics. It receives resources from the Oregon Health Authority by capitation payment through regionalized Coordinated Care Organizations (Oregon’s name for Accountable Care Organizations) and has a global budget.

#### Eligibility and recruitment

##### Selection of sites/clusters

In the 14 counties, ADS has a significant Medicaid market share (33 % to 100 %).

##### Selection of participants

The study population is approximately 82,000 children and pregnant women enrolled in Medicaid and living in the 14 counties. The inclusion criteria are as follows:Children younger than 21 years of age and women who are pregnant or up to 2 months postpartum.Enrollment in Medicaid and assigned to receive dental care from ADS.Home address is located in the selected counties.

The age distribution of the children is as follows: 0 to 5 years old, 36 %; 6 to 15 years old, 46 %; and 16 to 20 years old, 17 %. Twenty-one percent of the children and 11 % of the pregnant women are Hispanic, 5 % of children and 4 % of the pregnant women are from other minority races/ethnicities. All pregnant women, new mothers and children <21 years old are enrolled in Medicaid and the Children’s Health Insurance Program.

Recruitment: Participants are identified through a search of the ADS enrollment database. A random subsample of participants is recruited by telephone to participate in an evaluation of the services by completing a telephone survey. Passive informed consent for caries detection and risk assessment at community settings are obtained, as well as active informed consent for treatments provided at these settings.

#### Randomization and blinding

Each County is considered a single cluster. Clusters are randomized with equal probability to the test or control interventions, using computer-generated random numbers. The allocation schedule for random assignment is generated at the University of Washington by the project biostatistician. The treatment allocation for each cluster is kept in Seattle, and the biostatistician informs local investigators about the treatment allocation, when they are ready to conduct the environmental scan of the test sites. Interviewers are blinded to group allocation. Because of the type of the intervention, personnel involved in the delivery of the intervention and participants are not blinded to group allocation.

#### Timing of recruitment, intervention delivery and follow-up

Identification of the clusters (counties) and randomization to test and control interventions was concluded in October 2014. The first phase of the project has been initiated, including the rewriting of job descriptions, identification of appropriate staff members, refinement of outcome metrics, and initial development of IT systems to support the service delivery and incentive payment changes. Formal training of staff will begin in spring 2015; the implementation of the new delivery system will begin in summer 2015; full project implementation will begin when schools open in September 2015 and will last for 24 months. Baseline assessments will be conducted during summer and fall 2015 and final assessments during summer and fall 2017.

### Intervention

#### Development of the program and conceptual framework

We carried out a root cause analysis, based on our previous work on access barriers. We used data from surveys with dental care providers [15–17], pregnant women, new mothers and parents of schoolchildren [18–20] conducted over the past 10 years. Taken together, the major findings include: 1) significant knowledge differences among dentists and hygienists about caring for pregnant women [16] and preschool children [21]; 2) children who had a regular source of care had better oral health [20]; and 3) low-income pregnant women were unaware of Medicaid coverage and/or were uncertain of their acceptance in dental practices [18]. From this work, we created a behavioral model for the use of health services by vulnerable populations [22]. The model posits that disparities are rooted in the health care system and in the social and physical environments of people with fewer resources [23]. In addition to these contextual influences, personal- and family-level factors are important (for example, health beliefs, income, social support, source of care, and skills to navigate the dental system). Considerations of program reach, dental health urgency, cost, organizational readiness, and politics led us to a two-pronged intervention that affects the delivery and the payment systems. The drivers, core components and outcomes of the intervention were operationalized in a multi-level structure based on the Active Implementation Framework [24], and a logic model for the intervention was constructed (Fig. 1). The intervention includes changes at the provider, organization, and system levels and evaluation at the community and patient levels. In addition to program outcomes, we plan to evaluate the extent to which the intervention is delivered as planned.

**Fig. 1 Fig1:**
[figure not shown]
Program logic for PREDICT

#### PREDICT - the program

In the seven test counties, Expanded Practice Permit Dental Hygienists (EPPDH) will obtain the consent for treatment at community settings and provide selected primary dental services in non-traditional settings and refer patients to primary care dentists and specialists for complex treatments. Community liaisons and case managers, serving as patient navigators, will help the EPPDH obtain the consents and assure that needed treatments are completed at community and dental office settings. This new delivery system is supported by a financial incentive system for high performance (pay-for-performance, capitation payment and global budget) and by an efficient information system for performance monitoring. The service delivery and payment changes focus on the following: 1) identifying Medicaid-eligible children, pregnant women and new mothers and gaining caregiver consent for services in community settings (for example, schools, Head Start, and WIC Centers); 2) providing risk-based preventive and caries stabilization services efficiently at these settings; 3) providing seamless, effective curative care in dental clinics; and 4) incentivizing local delivery teams to meet performance benchmarks.

#### Control group

The control group consists of seven counties in which Medicaid-eligible low-income children and mothers receive dental care from ADS. This is a “usual care” control with an emphasis on clinic-based care; which includes preventive treatments (not risk based) at some community settings and curative care in dental offices. In the usual care condition the EPPDHs function in a conventional role. Incentives are largely for dentists and not for other team members.

### Study measures and data collection

The primary and secondary study measures for impact and process outcomes are presented in Table 1.

**Table 1 Tab1:** PREDICT study measures: impact and process outcomes

Type of outcome	Outcome measures	Description	Operationalization
Impact: primary	Oral health	Proportion of children with untreated dental caries	Number of Medicaid ADS-assigned children with untreated caries divided by the number of children enrolled in Medicaid and assigned to ADS.
Impact: secondary	Patient/consumer satisfaction	Mean quality of care	Mean score for the ratings of quality of care from the parent survey
Process: primary	Dental care utilization by children	Percentage of children who received a dental service	Number of Medicaid-enrolled ADS-assigned children who received a dental service (any CDT code) divided by the number of Medicaid-enrolled ADS-assigned.
Process: primary	Consent for treatment at community settings	Proportion of children for whom consent is obtained	Number of Medicaid ADS-assigned children for whom consent is obtained divided by the number of Medicaid ADS-assigned children.
Process: primary	Oral health screening and risk assessment	Proportion of children who received screening and risk assessment	Number of Medicaid-enrolled ADS-assigned children who received both a screening (CDT 0191) and a risk assessment (CDT 0601-D0603) divided by the number of Medicaid-enrolled ADS-assigned children.
Process: primary	Timely need-based curative treatments	Proportion of children referred for dentist treatment who receive care within 60 days of screening	Number of Medicaid-enrolled ADS-assigned children with dentist treatment needs who visited the dentist (CDT D1000 to D9999) within 60 days of screening divided by the number of Medicaid-enrolled ADS-assigned children with dentist treatment needs.
Process: primary	Dental care utilization by pregnant women and new mothers	Percentage of pregnant women and new mothers who received a dental service	Number of Medicaid-enrolled ADS-assigned pregnant women who received a dental service (any CDT code) divided by the number of Medicaid-enrolled ADS-assigned pregnant women and new mothers.
Process: secondary	Risk-based preventive treatments	Proportion of children at high or moderate risk who receive preventive services	Number of Medicaid-enrolled ADS-assigned children considered at high or moderate caries risk (CDT 0602 to D0603) who received any preventive service (CDT 1000 to 1999) divided by the number of Medicaid-enrolled ADS-assigned children considered at high or moderate caries risk (CDT code 0602 to D0603).
Process: secondary	Emergency Department Visit Rate	Percentage of participants who visited an Emergency Department for dental conditions	Number of Medicaid-enrolled ADS-assigned children and women who visited an ED for dental conditions (any CDT code) divided by the number of Medicaid-enrolled ADS-assigned children and women.

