#### Data collection

Data on *impact outcomes* will be obtained through a clinical examination of children and a telephone survey of parents/caregivers and children at baseline and after 24 months. A random sample of Medicaid-enrolled ADS-assigned children will be obtained and stratified by county, at baseline and 24 months post-implementation. The sample will include children whose caregivers either consented or did not consent for care. It will also include children who sought care directly from a dental office. For the survey, staff members will be given a list of enrollees to telephone and move down the list in order until the required sample size is reached. Each individual will be called a minimum of five times. For the clinical examination, staff members will be given a list of enrollees, and they will exam the children in the community settings.

Data on *process and cost outcomes* will be obtained through ADS’s health information systems: Medicaid enrollment database, ADS database (ADIN), electronic dental records and payroll ledger. All Medicaid-enrolled ADS-assigned children population will be included in the process and cost evaluation. Enrollment information including patient identifiers, birth date, gender, race/ ethnicity, coverage dates and assigned primary care provider will be obtained from ADS’s enrollment database and linked to State Medicaid claims. Medicaid claims will be accessed to collect emergency department, medical care and prescription services and costs. Data on *structure outcomes* will be obtained through staff online surveys at baseline and after 24 months and continuously through ADS’s health information systems and internal records. Fidelity information will be obtained through staff surveys and internal records.

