### Statistical analysis

#### Sample size

Based on seven test counties and seven control counties, the power is at least 80 % to detect an increase in dental care utilization from pre- to post-implementation within the test counties or an increase in utilization between test and control counties post-implementation of approximately 10 percentage points for utilization rates of 5 % to 10 %, 15 percentage points for utilization rates of 20 % to 30 %, and 20 percentage points for utilization rates of 40 % to 50 %. Estimates are conservative, based on an intracounty correlation (ICC) of 0.05. Pilot data on dental care utilization indicated ICCs were less than 0.05 for cluster sizes of 200 or more children, and ICCs were less than 0.02 for cluster sizes greater than 500 children. Using a sample size of 80 children per county pre- and post-implementation and an ICC of 0.05, we estimate power is 80 % to demonstrate a 15 percentage point or larger decrease in prevalence of untreated dental caries, assuming a prevalence of untreated caries of 25 % in the control counties. In 2012, 25 % of 6 to 10 years old from low-income families in Oregon had untreated dental decay [28]. Using a sample size of 20 parents per county pre- and post-implementation we estimate power is 84 %, based on a two-sided 0.05 significance level, to detect a medium effect of the intervention on dental care ratings (for example, an average increase of 0.75 points) (CAHPS; range 1 to 10), assuming SD = 1.5 in patient satisfaction scores [29].

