#### Statistical analysis plan

Descriptive statistics (means, standard deviations, counts, and percentages) are calculated for all variables of interest overall and stratified by age group. The primary hypothesis is that the test intervention participants will have lower number of untreated dental caries than the control participants and the absolute changes indicate a reduction in disparities. Multilevel regression are used to assess for changes in the impact and process outcomes between pre- and post-implementation in the test and control counties, weighted by the number of eligible children/pregnant women in the county at each time point and adjusting for within-county correlation between pre- and post-implementation outcomes [30]. We use multilevel linear regression for mean scores and multilevel binomial regression for binary measures. Additional multilevel regression modeling are used to compare changes in the impact and process outcomes by child age category (for example, 0 to 5, 6 to 15 and 16 to 20 years old) or race/ethnicity, adjusting for clustering within county and weighting by number of eligible children in each age or race/ethnicity category.

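### Table 1 divides the primary caries outcome by all enrolled children, which does not match the examined sample or the 25% prevalence used for power

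*Protocol article*

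**What the plan says.** All references are to the protocol article.

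- **Primary outcome.** In Table 1 (Study measures and data collection), the Operationalization column gives "Number of Medicaid ADS-assigned children with untreated caries divided by the number of children enrolled in Medicaid and assigned to ADS".
- **Data source.** Under Data collection, impact outcomes "will be obtained through a clinical examination of children and a telephone survey of parents/caregivers and children at baseline and after 24 months". The sampling rule is "A random sample of Medicaid-enrolled ADS-assigned children will be obtained and stratified by county, at baseline and 24 months post-implementation", and "For the clinical examination, staff members will be given a list of enrollees, and they will exam the children in the community settings". Only process and cost outcomes are assigned to the whole enrolled population.
- **Size.** The Sample size section reads "Using a sample size of 80 children per county pre- and post-implementation", with an ICC of 0.05, 25% untreated caries in control counties, a 15-point decrease and 80% power.
- **Hypothesis.** In the Statistical analysis plan section, test participants are expected to have a "lower number of untreated dental caries than the control participants". The Abstract, the main research question, Table 1 and the Sample size section all speak of a prevalence or proportion.
- **Objective.** Aims and objectives sets the primary objective as the "effectiveness of the new model on decreasing dental caries in Medicaid-enrolled children, pregnant women and new mothers".
- **Women's utilization**, a primary process outcome in Table 1: the number of "ADS-assigned pregnant women who received a dental service (any CDT code) divided by the number of Medicaid-enrolled ADS-assigned pregnant women and new mothers".

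**The concern.** The column headed Operationalization should tell an analyst what to divide by what. For the primary outcome it gives the denominator used in the process rows computed from records on every enrollee, yet caries status is known only for examined children. Other rows do name a restriction or a source where one applies: children with treatment needs, children at elevated risk, the parent survey. The caries row does not.

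At stake is whether the reported primary outcome is a prevalence at all. The cost-effectiveness ratio inherits the problem, because its denominator is the between-arm difference in the proportion with untreated caries. The hypothesis and objective add to the uncertainty, since one names a different quantity and the other a wider population than the outcome table.

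**Working it through.** **Inputs.** 7 test and 7 control counties, 80 children per county per round, ICC 0.05, 25% versus 10% (a 15-point fall), power 80% (all Sample size); about 82,000 children and pregnant women (Selection of participants). Two-sided 0.05 is stated only for the parent survey and is assumed here for caries. The number of children alone and the enrolment by county are not given.

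**1. Reproduce the plan's figure, with examined children as denominator.**
- Design effect: 1 + (80 − 1) × 0.05 = 4.95.
- Two proportions, 25% versus 10%, 80% power, continuity-corrected: 113 per arm before clustering.
- Per county: 113 × 4.95 / 7 = 79.9, against 80 stated.
- Power at an effective 560 / 4.95 = 113.1 per arm: 0.848 by pooled z and 0.794 by t with 12 degrees of freedom, unpooled.

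The stated 80 per county and 80% power stand.

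**2. Apply the Table 1 formula literally to the same data.** Equal enrolment is assumed for illustration.
- Enrollees per county: 82,000 / 14 = 5,857.
- Share examined, which is also the largest value the ratio can take: 80 / 5,857 = 1.37%.
- Control at 25%: 20 / 5,857 = 0.34%. Test at 10%: 8 / 5,857 = 0.14%.
- The 15-point difference becomes 12 / 5,857 = 0.20 points, smaller by a factor of 5,857 / 80 = 73. A cost-effectiveness ratio built on it would be about 73 times larger.

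The 82,000 includes pregnant women. A children-only count would raise these percentages somewhat without changing the conclusion.

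**3. Dependence on enrolment.** Take a true prevalence of 25% in both arms and 560 examined per arm, so 140 cases each.
- Enrolment split 41,000 / 41,000: 0.34% versus 0.34%.
- Enrolment split 50,000 / 32,000 (assumed): 140 / 50,000 = 0.28% versus 140 / 32,000 = 0.44%.

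Weighting by eligible children does not remove this. If county c contributes x_c / N_c with weight N_c, the weighted mean is Σx_c / ΣN_c, which is the figure just shown.

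**4. Dependence on numbers examined.** Equal enrolment, true 25% in both arms; unequal counts are an assumption, since the plan is 80 everywhere.

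| Examined per county | Table 1 denominator | Examined as denominator |
|---|---|---|
| 80 vs 80 | 0.34% vs 0.34% | 25% vs 25% |
| 80 vs 64 | 0.34% vs 0.27% | 25% vs 25% |
| 80 vs 40 | 0.34% vs 0.17% | 25% vs 25% |

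The last column assumes that those examined represent those sampled.

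**5. Linked statements.**
- *Hypothesis.* A number of caries and a proportion of children with caries are different outcomes: the first can fall while the second does not. The Statistical analysis plan section offers linear models for mean scores and binomial models for binary measures, which fits the proportion.
- *Objective.* Examinations are planned for children only, and Table 1 has no caries measure for women.
- *Women's rate.* Let s be the share of new mothers in the denominator, and r_p and r_m the utilization of pregnant women and new mothers. The printed formula gives r_p(1 − s); the rate named in the row's label is r_p(1 − s) + r_m·s. The shortfall is r_m·s, so new mothers can only lower the printed rate. The documents do not give s.

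**The case against.** Numerator and denominator in Table 1 name the same population, and the Description column calls the measure a proportion of children. That can be read as an ordinary population prevalence, which the random sample then estimates. The power calculation uses 25%, and the weights by eligible children suit the projection of sample estimates to enrollees. A value below 1.4% would also look wrong to anyone who knew the planning figure. This reading is probably what was intended, and it stands as an account of intent. It does not make the printed formula computable from the planned data.

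Two stronger readings are tempting. A reader might infer that unexamined children are to be counted as caries-free. No section says so; it follows only from applying the formula literally to a sample. A reader might also infer that screening records would feed the numerator, so that heavier screening in test counties would look like more caries. Data collection assigns impact outcomes to the examination and the survey of a random sample, which includes non-consenters and children who went directly to a dental office. Only process and cost outcomes come from the organization's records. The documents do not support that scenario.

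The linked inconsistencies can fairly be called editorial. Table 1 already limits the primary caries outcome to children, and most of the article says prevalence. They still sit in the primary objective, the primary hypothesis and a primary process outcome.

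**Conclusion.** The concern holds as a mismatch in the definition of the primary outcome. The printed denominator is all enrolled children; the data source and the power calculation use about 80 examined children per county per round. Taken literally, the ratio is capped at about 1.4% (assuming equal county enrolment and 82,000 as the base), varies with enrolment, and cannot show the 25% or the 15-point difference that the trial is planned around.

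The sample size is unaffected, and nothing shows that the authors intend the literal calculation. Bias between arms would need the literal formula together with unequal enrolment or unequal numbers examined; the article establishes neither.

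The hypothesis, the objective and the women's utilization row contradict other parts of the article as printed. The women's rate is understated by r_m·s, a size that the documents do not allow to be fixed.

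**What to change.** 1. In Table 1, define the primary outcome as sampled children with untreated caries at examination divided by sampled children examined, per county and round, weighted to enrolled children as the Statistical analysis plan section already provides. Enrolled children can remain the stated target population, provided the row says the proportion is estimated from the examined sample.
2. State the primary hypothesis as a lower proportion of children with untreated caries in test than in control counties.
3. Limit the caries part of the primary objective to children.
4. In the women's utilization row, count pregnant women and new mothers in both numerator and denominator.

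The cost is wording in Table 1, the hypothesis and the objective. No new data and no change in sample size are needed.

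### The primary process measure of timely curative treatment accepts preventive codes, and its operationalization does not state how a dentist visit is identified

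*Protocol article*

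**What the plan says.** Table 1 (Study measures and data collection) has a row of type primary process outcome named "Timely need-based curative treatments". Three parts of the row matter:

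- **Description:** "Proportion of children referred for dentist treatment who receive care within 60 days of screening". The kind of care is not restricted.
- **Numerator:** children with dentist treatment needs who "visited the dentist (CDT D1000 to D9999) within 60 days of screening".
- **Denominator:** all enrolled, assigned children with dentist treatment needs.

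A later row of the table, on risk-based preventive treatments, counts children "who received any preventive service (CDT 1000 to 1999" and so fixes what the article means by a preventive code.

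On delivery, the Abstract says of the test counties that "allied dental personnel provide screening and preventive services in community settings". The section on the PREDICT program adds "providing risk-based preventive and caries stabilization services efficiently at these settings" as an aim for those settings and says that the hygienists "refer patients to primary care dentists and specialists for complex treatments". Usual care, in the Control group section, includes "preventive treatments (not risk based) at some community settings and curative care in dental offices".

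**The concern.** Of the process outcomes in Table 1, this is the one that asks whether children found to need a dentist receive that care promptly. The Discussion names this step as one of the programme's challenges. A measure that preventive services can satisfy does not answer the question.

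There are two layers. The first is certain: the name says curative, but the codes admit preventive care. The second is conditional: if the claims query applies the codes without a provider condition, a hygienist's preventive service at a school would be recorded as a dentist visit. The intervention itself supplies such services, so the error would differ between arms and could show successful referral where referral had failed.

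**Working it through.** The article gives no rate, power or target for this measure, so there is no planned figure to reproduce. The check has two parts.

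**1. Code ranges side by side (both from Table 1)**

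| Row | Codes counted |
|---|---|
| Timely need-based curative treatments | D1000 to D9999 |
| Risk-based preventive treatments | 1000 to 1999 |

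Every code in the second range is in the first. The lower limit of D1000 removes only codes below 1000, such as the screening code (0191) and the risk assessment codes (0601 to 0603) used elsewhere in the table. It removes nothing that the table calls preventive.

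**2. What a codes-only query would do**

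Let p be the true share of children in need who are seen by a dentist within 60 days. Let q be the share of the remaining children who have a preventive code from another provider in that window. Then:

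- measured rate = p + (1 − p)q
- spurious difference, with the same p in both arms = (1 − p)(q_test − q_control)

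None of the values of p and q below is in the article. All are assumptions.

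| p (both arms) | q test | q control | Measured, test | Measured, control | Spurious difference |
|---|---|---|---|---|---|
| 0.60 | 0.20 | 0.05 | 0.60 + 0.40 × 0.20 = 0.68 | 0.60 + 0.40 × 0.05 = 0.62 | 6 points |
| 0.40 | 0.50 | 0.10 | 0.40 + 0.60 × 0.50 = 0.70 | 0.40 + 0.60 × 0.10 = 0.46 | 24 points |
| 0.30 | 0.80 | 0.10 | 0.30 + 0.70 × 0.80 = 0.86 | 0.30 + 0.70 × 0.10 = 0.37 | 49 points |
| 0.40 | 0.30 | 0.30 | 0.40 + 0.60 × 0.30 = 0.58 | 0.40 + 0.60 × 0.30 = 0.58 | 0 points |

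A dentist filter sets q to 0 in both arms and also gives a difference of 0. It would still count a dentist's preventive service as curative.

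The direction follows from the delivery model. Community preventive care by hygienists is a core part of PREDICT. In control counties it occurs at some community settings only, and the hygienists keep a conventional role. Comparing pre- to post-implementation changes, as the Statistical analysis plan section intends, would not remove the error, because this exposure would rise in the test counties when the programme starts.

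**The case against.** The strongest reply is that the numerator says the child visited the dentist, and the description limits the measure to children referred for dentist treatment. The program section also separates the hygienist, who treats and refers, from the dentist. Applied as written, those words exclude hygienist services. The differential bias then disappears, and the article gives no reason to think that preventive services by dentists would favour one arm. How a visit is found in claims may also be a detail for a fuller plan that is not shown.

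Much of this stands. A reader might infer that hygienist services certainly count as dentist visits; the article does not establish that. What the reply does not remove is the code range. The article states it explicitly, and it conflicts with the name of the measure whoever the provider is.

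Three further inferences are tempting and unsupported:

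- **That the test arm could approach 100% without curative care.** No rate in the article supports this. Community treatment needs active consent, and the Discussion lists parent sign-up as a major challenge.
- **That control counties contribute mainly children already in a dental office, so the denominators differ in a known way.** No section says so. What can be said is narrower: the 60-day clock starts at screening, which PREDICT is designed to increase.
- **That the random examination sample offers a cleaner denominator.** Examinations take place only at baseline and 24 months, so a 60-day follow-up would miss most of the programme. Children still with untreated caries at 24 months are themselves selected by the intervention. Numbers would be small: 7 counties × 80 × 0.25 = 140 per arm, or 7 × 80 × 0.10 = 56 in the test arm under the planned 15-point reduction, before any allowance for clustering.

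**Conclusion.** The measure is wrong as written in one definite respect: codes that Table 1 calls preventive satisfy an outcome named curative. A bias in favour of PREDICT is plausible but conditional. It requires that the query use codes alone and that preventive exposure among children not seen by a dentist be higher in test counties. Its size cannot be derived from the article. Under the assumed values it runs from 0 to 49 percentage points, and any single figure in that range is an illustration only.

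This should be fixed, but it does not threaten the trial's main conclusion. The primary outcome is untreated caries assessed by clinical examination, and no sample size statement depends on this measure.

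**What to change.** In the Table 1 row:

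1. Exclude codes 1000 to 1999 from the numerator.
2. State that the rendering provider must be a dentist, so that hygienist community services do not count. This is needed as well as the code change, because PREDICT also delivers caries stabilization at community sites and the article does not say how those services are coded.

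The between-arm result should carry a caution that its denominator depends on screening, which the intervention aims to expand.

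The cost is one table row and one change to the claims query. Reported rates will be somewhat lower, because visits with only preventive codes no longer count.
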